### Assignment of interventions: blinding

#### Who will be blinded {17a}

Due to the nature of the intervention, the allocation cannot be masked neither for participants nor for physicians or data managers

#### Procedure for unblinding if needed {17b}

Not applicable, no blinding.

### Data collection and management

#### Plans for assessment and collection of outcomes {18a}

A dedicated electronic case report form (e-CRF) within Ennov Clinical® software was created and managed by Clinical Research Department, Hospices Civils de Lyon. The following data are collected upon inclusion: demographics, type of surgery, type of anesthesia, assessment of neuropathic pain with DN4, and assessment of the sleep quality with PSQI. After the discharge, patients fill in the dedicated diary. The prevalence of severe pain (which patients deem to be important) (binary), pain relief (continuous), painkiller administration (binary), and side effects from painkiller (binary) are collected in a time-dependent manner with 30 min grid over 24 h. On day 30, patients fill in the assessment of neuropathic pain with DN4, assessment of the sleep quality with PSQI, and the International Pain Outcome questionnaire (multiple binary, categorical and continuous variables). After the diary completion, patients were asked to send the collected data to the investigators.

#### Plans to promote participant retention and complete follow-up {18b}

After the inclusion and discharge from the hospital, patients receive a short text message and/or e-mail reminders to complete the follow-up on days 0, 1, 2, 3, 4, 5, 10, 20, and 30 post-discharge. A postal stationery envelope (prepayment of postage) with the printed investigator’s return address is given to each patient along with the diary. Patients are invited to return their diary via the post service, or they may bring it to the hospital. Two weeks following the end of study, if there is no diary return, the patient is contacted by the associate research coordinator and invited to send the diary to the investigator.

#### Data management {19}

Upon each diary reception, all data are transcribed to the e-CRF by a dedicated Clinical Research Associates from Clinical Research Department, Hospices Civils de Lyon. The quality of collected data is verified upon monitoring visits. After the study completion, all data will undergo the quality check by the Data Manager. All collected data are confidential and anonymized. Only the principal investigator has access to the de-anonymization tables.

#### Confidentiality {27}

All study-related information is stored in the secured institutional Electronic Health Record system and electronic Clinical Research Form system *Ennov*, controlled by our institution. The access to both systems is controlled. All study-related data are pseudo-anonymized, and the deanonymization list is encrypted, stored separately, and available only for investigators.

#### Plans for collection, laboratory evaluation, and storage of biological specimens for genetic or molecular analysis in this trial/future use {33}

Not applicable; no biological sampling nor laboratory investigation is planned for this study.

### Statistical methods

#### Statistical methods for primary and secondary outcomes {20a}

Analyses will be performed on an intention-to-treat basis. All data will be checked for normal distribution, and variables will be presented as mean ± standard deviation (SD) or as the median and interquartile range [IQR] accordingly. Categorical variables will be presented as the number and percentage of the total. To compare the two groups, we will use Fisher’s exact test for qualitative data and the non-parametric Mann-Whitney tests for quantitative variables. A comparison of the two groups at randomization will identify potential bias due to unequal allocation. A multivariate logistic regression analysis will be performed to study conditions independently associated with the response to the intervention and to control potential confounding factors. A 0.05 *p* value will indicate statistical significance. Statistical analyses will be performed using R software (R Foundation for Statistical Computing, Vienna, Austria).

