### Sample size {14}

In the beginning of our study, we were not able to identify any randomized study of educational intervention with TOTPAR as a primary endpoint. It has been reported, that more than 30% of orthopedic patients suffer from “important” pain (e.g., >6/10) during the first 72 h post-discharge [41, 42]. A 2-point change in the 11-item scale or 30% of the difference in pain intensity measurement is defined as clinically significant [43].

We analyzed the literature, reporting the effect of preoperative education on postoperative orthopedic pain in outpatient settings, and available on the year of the study development. Two studies reported the clinically significant effect from the preoperative education, with calculated OR 1.77 [95%CI 1.12–2.79] to 1.97 [95%CI 1.09–3.57] [44, 45]. However, the quality analysis of these studies demonstrated important heterogeneity, the absence of power calculation, small clinical effects, and design flaws.

As we were not able to find any relevant data for the sample size calculation, we have arbitrarily chosen the OR=2 from the effect of preoperative education, which will produce the decrease of proportion of patients with “important” pain from 30 to 17.6%. Giving this assumption, with the risk alpha of 5% and the power at 80%, allocation 1:1, the calculated sample size was 368 patients. We estimate the loss to follow-up at 10%, therefore the 410 patients will be finally enrolled.

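### The 80% power quoted for 30% versus 17.6% fits an uncorrected two-proportion calculation; the Fisher's exact test assigned to binary data gives about 77% at 368 patients

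*Protocol article*

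**What the plan says.** The section Sample size {14} works from a binary endpoint, the share of patients with important pain. It takes a control rate of 30% and says of the effect: "we have arbitrarily chosen the OR=2 from the effect of preoperative education". That gives 17.6% in the educated arm. The result is stated as "with the risk alpha of 5% and the power at 80%, allocation 1:1, the calculated sample size was 368 patients". The section does not name the test behind this number or say whether alpha is one- or two-sided. Allowance for attrition follows: "We estimate the loss to follow-up at 10%, therefore the 410 patients will be finally enrolled".

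The section Statistical methods for primary and secondary outcomes {20a} compares the arms using "Fisher’s exact test for qualitative data" and Mann-Whitney tests for quantitative variables. Fisher's test carries no condition about small cells. The only other method there that could apply to a binary outcome is a multivariate logistic regression, intended for factors associated with response and for confounders.

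The section Outcomes {12} makes TOTPAR over 5 days, a quantitative measure, the primary outcome. Severe pain, as judged by the patient, is a secondary outcome.

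**The concern.** A power statement holds only for the test that will be run. Fisher's exact test conditions on the margins of the table and, because its p-value is discrete, usually rejects less often under the null than its nominal level allows. With arms of this size it therefore has less power than the uncorrected chi-square test. If 368 came from an uncorrected formula, the article claims a power that its named test does not reach. What is at stake is a few points of power on the binary pain comparison, given up where the cell counts are large enough that exactness is not needed for type I error control.

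**Working it through.** **Inputs.** From Sample size {14}: control rate p1 = 0.30, educated-arm rate p2 = 0.176, alpha 0.05, power 0.80, allocation 1:1, 368 evaluable (184 per arm), 10% loss. From Statistical methods {20a}: Fisher's exact test, significance at 0.05, analysis in R. Assumption: two-sided testing, since only that reproduces 368.

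**Step 1: the second rate.** The control odds are 0.30/0.70 = 0.4286. Halved, they are 0.2143, so p2 = 0.2143/1.2143 = 0.17647, which the article rounds to 17.6%.

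**Step 2: reproduce 368.** The uncorrected formula with pooled variance under the null is

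n per arm = [1.960·√(2·p̄·(1−p̄)) + 0.842·√(p1(1−p1) + p2(1−p2))]² / (p1−p2)²

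with p̄ = (0.30 + 0.176)/2 = 0.238.

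- First term: 1.960·√(2·0.238·0.762) = 1.960·√0.36271 = 1.1804
- Second term: 0.842·√(0.2100 + 0.1450) = 0.842·√0.3550 = 0.5015
- n = (1.6819)² / (0.124)² = 2.8287/0.015376 = 183.97, so 184 per arm and **368 in total**, an exact match.

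Other two-sided versions at 17.6% give 364 (unpooled variance), 366 (arcsine) and 400 (continuity-corrected, the usual approximation to Fisher's test). One-sided versions give 290 uncorrected and 322 corrected. With the unrounded 17.647%, the pooled formula gives 372 and the arcsine formula 368. Every version close to 368 is uncorrected.

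**Step 3: power of each test at 184 per arm.** Power is the sum, over all pairs of event counts (x, y), of Bin(x; 184, p1)·Bin(y; 184, p2) for those pairs where the test gives p ≤ 0.05. Fisher's two-sided p-value uses the probability-ordering rule of R's `fisher.test`; doubling the one-sided p-value gives the same power.

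| Per arm | p2 | Fisher | Pearson chi-square |
|---|---|---|---|
| 184 | 0.176 | 76.8% | 80.3% |
| 184 | 0.17647 | 76.5% | 80.0% |
| 198 | 0.176 | 80.1% | 83.1% |
| 200 | 0.17647 | 80.1% | 83.2% |
| 205 | 0.176 | 81.4% | 84.5% |

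The shortfall from the stated 80% is 80.0 − 76.8 = 3.2 points, or 80.0 − 76.5 = 3.5 points at an odds ratio of exactly 2.

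**Step 4: actual type I error at 184 per arm.** With a common rate of 23.8%, Fisher's test rejects in 3.8% of trials and the chi-square test in 5.0%. At a common rate of 30% the figures are again 3.8% and 5.0%.

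**Step 5: what 80% would take with Fisher's test.** It needs 198 per arm at 17.6%, or 200 per arm at 17.647%, which is 396 to 400 evaluable. That is 28 to 32 more than 368. With 10% loss, 396/0.9 = 440 and 400/0.9 = 444.4, so about 440 to 445 enrolled against the stated 410.

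**Step 6: is exactness needed here?** The expected number of events per arm under the null is 184·0.238 = 43.8, far above the range where the chi-square approximation is in doubt.

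**The case against.** The strongest objection is relevance. The sizing comparison (pain above 6 out of 10 in the first 72 hours) is not a listed outcome. The nearest one, patient-defined severe pain, has no numeric cut-off and, according to the abstract, runs over 30 days, so the 30% and 17.6% rates need not apply to it. This stands, and it limits the point to the sizing comparison and, by extension, that secondary outcome.

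A reader might infer that the primary analysis is underpowered because of Fisher's test. The documents do not support that: TOTPAR is quantitative and would go to Mann-Whitney. That the sample-size calculation does not involve TOTPAR at all is a separate and larger problem. If the trial were re-sized on TOTPAR, the 80% and 368 would be replaced, and only the choice of test for binary outcomes would remain.

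A reader might also infer that precision is lost. It is not: the choice between Fisher and Pearson alters the p-value, not the estimated difference or its standard error.

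Fisher's test is a valid choice that controls type I error, so naming it is not a mistake in itself. The uncorrected origin of 368 is inferred from a numerical match. Both remarks are fair, but neither removes the mismatch: however 368 was derived, Fisher's test gives about 77% there.

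The gap is also small beside an odds ratio that the article itself calls arbitrary, and if all 410 enrolled patients were evaluable, Fisher's power would be 81.4%. The first remark stands and keeps the point minor. The second does not rescue the stated figure, because the extra patients are there to cover the expected loss.

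**Conclusion.** The point holds as a minor inconsistency. At 368 evaluable patients, the only two-group test named for qualitative data has 76.5% to 76.8% power for the sizing comparison, not 80%, and an actual type I error of about 3.8%. Pearson's chi-square test has about 80% and 5.0%. This rests on two-sided testing at 5%, equal arms of 184, no stratification in the test, and the article's own rates (17.6%, or 17.647% unrounded). It says nothing about the power of the primary TOTPAR test.

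**What to change.** In Statistical methods {20a}, name the uncorrected Pearson chi-square test for binary outcomes, or a Mantel-Haenszel or logistic analysis using the randomisation strata (type of surgery and type of anaesthesia). Keep Fisher's exact test for tables with small expected counts, for example any below 5.

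If Fisher's test is kept throughout, state in Sample size {14} that power for the binary comparison is about 77% at 368 evaluable patients, and that this is not the power of the primary TOTPAR test. Without that second statement, the corrected number would lend more weight to a calculation that does not concern the primary outcome.

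The cost is one sentence and no patients or data. The change should be a dated, documented amendment made before analysis. The trial is open-label, data managers included, and 256 patients had been recruited at the time of the article, so a later move to a less conservative test could look driven by results. No interim analysis is planned, which makes a clean change feasible.

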### Outcomes {12}

The primary outcome is the pain relief measured with a percentage of maximum total pain relief (TOTPAR) over 5 days. TOTPAR is a time-weighted measure of total area under the pain relief curve. This measurement assimilates iterative assessments of a subject’s pain over the duration of the study.

The secondary outcome includes:TOTPAR at day 10, day 20, and day 30 after surgeryThe incidence of severe pain (defined as “severe pain” by the patient)Type, quantity, and doses of taken analgesicsNeuropathic pain prevalence at day 30, detected with DN4 scale [38]The sleep quality measured with Pittsburgh Sleep Quality Index (PSQI) [39] and compared at inclusion day and at the 30th postoperative dayPatients’ perception of postoperative pain management evaluated at with the International Pain Outcome (IPO) questionnaire [40] on day 30 after surgery

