### Assignment of interventions: allocation

#### Sequence generation {16a}

Enrolled patients will be randomly assigned to a control or interventional group with a 1:1 allocation using Ennov Clinical® software (Paris, France) with an embedded IWRS (Interactive Web Response System) randomization system. Patients will be stratified by the type of surgery (knee, hip, or shoulder isolated arthroscopy, MPFL, Kenneth Jones or Hamstring anterior cruciate ligaments repair, posterior cruciate ligaments repair, Latarjet open shoulder procedure, and video-assisted rotator cuff repair) and type of anesthesia (spinal, general, combined general and regional anesthesia). The configuration of the randomization and the implementation of the randomization list in the software were made by the statistician who is not involved in the process of patient inclusion and randomization. The list was created with variable block size using nQuery Advisor®, 7.0 (Statistical Solutions Ltd, Cork, Ireland). No one, except the statistician, has access to the randomization list.

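### The primary TOTPAR test leaves out the surgery and anaesthesia strata used in randomisation; it stays valid but is conservative if those strata predict pain relief, and adjusting for them is free

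*Protocol article*

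**What the plan says.** The article's Outcomes {12} section defines a quantitative primary endpoint: "The primary outcome is the pain relief measured with a percentage of maximum total pain relief (TOTPAR) over 5 days".

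Sequence generation {16a} states "Patients will be stratified by the type of surgery" and goes on to name nine procedures, if each listed operation is one level. The second factor is "type of anesthesia (spinal, general, combined general and regional anesthesia"), three levels. On blocking it says "The list was created with variable block size"; the sizes are not given.

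Statistical methods {20a} names two between-group tests: Fisher's "exact test for qualitative data", and "the non-parametric Mann-Whitney tests for quantitative variables". Neither carries a stratum or baseline term. The same section adds a multivariate logistic regression for response to the intervention and for confounding, without naming covariates. Section {20b} plans no additional analyses.

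For the two scales with a baseline, section {18a} records at inclusion "assessment of neuropathic pain with DN4, and assessment of the sleep quality with PSQI", and both are repeated on day 30. Outcomes {12} describes PSQI as "compared at inclusion day and at the 30th postoperative" day, and Objectives {7} speaks of changes in sleep quality. DN4 is defined as a day-30 prevalence, with no stated use of its inclusion value.

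**The concern.** The analysis does not follow the randomisation. With permuted blocks inside each stratum, the arms are nearly balanced on surgery and anaesthesia type by construction, so the real sampling variance of the arm difference contains little of the variation between strata. The Mann-Whitney test takes its variance from the pooled ranks and still includes that variation. If the strata are prognostic, its standard error is too large: the true type I error falls below 5% and some power is given away.

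The logistic regression does not close the gap. It models a binary response for which no definition is given, while TOTPAR is continuous, and it does not mention the stratification factors.

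Power on the primary outcome is at stake in a trial whose assumed effect (OR = 2) the article itself calls arbitrary, and which expects to need at least 48 months to recruit. A smaller, related matter is that the inclusion values of PSQI and DN4 could sharpen their day-30 comparisons.

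**Working it through.** **1. The plan's own figure.** Sample size {14} uses 30% versus 17.6%, alpha 5%, power 80%, 1:1. With the pooled-variance formula, two-sided, mean proportion 0.238:

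n per arm = [1.96·√(2·0.238·0.762) + 0.842·√(0.30·0.70 + 0.176·0.824)]² / 0.124² ≈ 184, so 368 in total. The stated 368 reproduces. It is the power of a comparison of two proportions with important pain. The article gives no effect or SD for TOTPAR, so the 80% below is only a reference point.

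**2. Inputs.** N = 368 and the 9 × 3 = 27 possible strata come from the article; 368/27 is about 14 patients per cell. R2, the share of TOTPAR variance explained by the strata, is assumed. Block sizes are assumed in the simulations.

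**3. Large-sample formulas.** Choose an effect for which a test with no prognostic strata has 80% power, so the expected z is 1.96 + 0.842 = 2.802. Under stratified randomisation the variance of the arm difference shrinks by (1 − R2), but the unstratified test does not use this.

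- True type I error, unstratified: 2·[1 − Φ(1.96/√(1 − R2))]
- Power, unstratified: Φ(0.842/√(1 − R2))
- Power, adjusted: Φ(2.802/√(1 − R2) − 1.96)

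| Assumed R2 | True type I, unstratified | Power, unstratified | Power, adjusted | Gain (points) |
|---|---|---|---|---|
| 5% | 4.4% | 80.6% | 82.0% | 1.4 |
| 10% | 3.9% | 81.3% | 84.0% | 2.7 |
| 20% | 2.8% | 82.7% | 88.0% | 5.3 |
| 30% | 1.9% | 84.3% | 91.8% | 7.5 |

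Unstratified power also rises with R2, because the stratified design itself reduces the variance. The gain must be counted from that column, not from 80%.

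**4. Simulation with rank tests.** N = 368, 27 uneven strata, permuted blocks of 2, 4 and 6 within strata, effect 0.299 SD, 4,000 runs per setting (Monte Carlo SE about 0.35 points at the null and 0.6 for power). Plain Mann-Whitney against a van Elteren test on all 27 cells:

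| Assumed R2 | Type I, Mann-Whitney | Type I, van Elteren | Power, Mann-Whitney | Power, van Elteren |
|---|---|---|---|---|
| 0 | 5.4% | 5.1% | 79.4% | 76.1% |
| 5% | 5.0% | 5.4% | 79.6% | 78.7% |
| 10% | 4.2% | 5.1% | 80.4% | 81.6% |
| 20% | 2.9% | 4.5% | 81.5% | 85.2% |
| 30% | 2.1% | 5.4% | 83.4% | 89.8% |

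The gain is about 1, 4 and 6 points at R2 of 10%, 20% and 30%. At 5% or less, the 27-cell test loses 1 to 3 points because the cells are thin. A separate simulation at R2 = 20% (3,000 trials, blocks of 4 and 6, d = 0.30) gave type I error of 3.0% unadjusted and 5.0% adjusted, and power of 82% and 87%.

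**5. Baselines.** For a continuous score with baseline correlation r (assumed), the variance of ANCOVA relative to a change score is (1 − r²)/[2(1 − r)] = (1 + r)/2. This is 0.65, 0.75 and 0.85 at r = 0.3, 0.5 and 0.7, a saving of 35%, 25% and 15%. The type I error is nominal with or without the baseline. The documents offer nothing from which to put a figure on DN4.

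**The case against.** The strongest reply is that nothing here is invalid. An unstratified test after stratified randomisation errs only on the safe side, and the cost may be nil: all patients receive the same analgesic prescription, and no figure in the article shows that pain relief differs by stratum. That stands, and it limits the point to an improvement.

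Four stronger readings are tempting and are not supported:

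- **That false positives are inflated.** Both the formula and the simulations show the error rate at or below nominal, apart from Monte Carlo noise. Omitting the PSQI or DN4 baseline leaves it nominal.
- **That PSQI ignores its baseline.** The article defines it as a comparison with inclusion, or a change. Only the choice between a change score and ANCOVA is open.
- **That the strata were chosen because they drive pain.** Section {16a} gives no reason, and Eligibility {10} says only that these operations, taken together, are painful.
- **That adjustment lifts a planned 80% to 84%, 88% or 92%.** The 80% belongs to a binary endpoint, and unstratified power under this design would itself be about 81%, 83% and 84%.

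One might also object that the article names no effect estimate for the primary outcome. That is commonly left to the full protocol or analysis plan, neither of which is shown, so it is not counted against the plan. The test itself is stated, so its mismatch with the randomisation can be judged.

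**Conclusion.** The point holds in limited form. The stated primary test does not account for the two factors used to stratify randomisation, and no other stated analysis of TOTPAR does. If the strata predict pain relief, the test is conservative: about 4%, 3% and 2% true type I error at R2 of 10%, 20% and 30%, with roughly 1-3, 4-5 and 6-7.5 points of power forgone. Each range runs from the 27-cell rank test to the large-sample adjusted test. At R2 of 5% or less, little or nothing is lost. The direction is certain given blocked randomisation within strata; the size rests on assumed R2 values and on a reference effect that the article does not supply for TOTPAR. The PSQI and DN4 part concerns precision only. This is a free improvement.

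**What to change.** - **Primary analysis:** rank ANCOVA or a linear model of percent maximum TOTPAR on arm, with surgery type and anaesthesia type as main effects and sparse procedure levels pooled by a rule set before the data are seen. Main effects need at most 8 + 2 = 10 stratum terms instead of 26, which avoids most of the thin-cell loss. A van Elteren test with merged cells is an alternative.
- **Reporting:** give the adjusted difference with its 95% CI, and keep the plain Mann-Whitney as a sensitivity analysis.
- **PSQI:** ANCOVA of the day-30 score on inclusion PSQI, arm and the strata.
- **DN4:** logistic regression of day-30 status on arm, inclusion DN4 and the strata.

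The cost is a few lines in the analysis plan and standard R code, fixed before the data are analysed. Surgery type, anaesthesia type, PSQI and DN4 are already collected at inclusion, and the sample size need not change.

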#### Methods for additional analyses (e.g., subgroup analyses) {20b}

No additional analyses are planned.

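### The only confounder-adjusted model is a logistic regression on an undefined response, so the continuous primary outcome either has no adjusted analysis or must be cut at an unstated point

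*Protocol article*

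**What the plan says.** The Outcomes section {12} states: "The primary outcome is the pain relief measured with a percentage of maximum total pain relief (TOTPAR) over 5 days". The data collection section {18a} gives the variable type in its list of diary items: "pain relief (continuous".

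The statistical methods section {20a}, which covers primary and secondary outcomes together, does three things that matter here:

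- It compares the arms using "non-parametric Mann-Whitney tests for quantitative variables", with Fisher's exact test for qualitative data. Neither test is adjusted.
- It gives the baseline table a diagnostic role: "A comparison of the two groups at randomization will identify potential bias due to unequal allocation".
- It names one multivariable model: "A multivariate logistic regression analysis will be performed to study conditions independently associated with the response to the intervention". The same sentence adds that the model serves "to control potential confounding factors".

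The section on sequence generation {16a} says: "Patients will be stratified by the type of surgery", and adds type of anaesthesia as a second factor. Neither factor is named in the analysis text. The section on additional and subgroup analyses {20b} says: "No additional analyses are planned".

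**The concern.** A logistic model needs a categorical outcome, and the primary outcome is a continuous score. The article sets no TOTPAR value that counts as a response. The sample size section {14} gives a threshold of 2 points or 30%, but for pain intensity. The Discussion mentions a clinically significant threshold without giving a value.

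Two readings remain. The logistic model may belong to some other, binary outcome, in which case the primary outcome has no adjusted analysis and the stratification factors are used nowhere. Or the model is meant for TOTPAR, in which case the score must be dichotomised at a point the article does not state. Participants, physicians and data managers all know the allocation {17a}, so a cut-off settled late could be settled with knowledge of the arms. The adjusted odds ratio would also answer a different question from the rank comparison, and the two could disagree because of the cut-off alone.

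Two smaller problems sit beside this. Under sound central randomisation, baseline differences arise by chance, so comparing the arms at baseline is a poor detector of allocation bias. And factors associated with response to the intervention, read literally, are effect modifiers. Those need arm-by-factor terms, which sit awkwardly with {20b}.

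**Working it through.** **The plan's own figure.** Section {14} assumes 30% with important pain and an odds ratio of 2. The odds become (0.30/0.70)/2 = 0.214, a proportion of 0.176. With two-sided alpha of 5% (the article does not state sidedness), 80% power and pooled variance:

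n per arm = [1.96·√(2 × 0.238 × 0.762) + 0.842·√(0.30 × 0.70 + 0.176 × 0.824)]² / 0.124² = 184, so 368 in total.

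Allowing 10% loss, 368/0.90 = 409, against 410 stated. The figure reproduces. It concerns a binary pain-intensity endpoint, so it says nothing about power for TOTPAR. Below it supplies only the number per arm.

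**Information kept after dichotomising.** No SD or shape for TOTPAR is given, so the shape is an assumption. For a normal outcome cut so that a fraction p falls on one side, the efficiency relative to a linear model is φ(z_p)²/[p(1−p)]. At the median this is 0.3989²/0.25 = 2/π = 0.637. Mann-Whitney has efficiency 3/π against the linear model, so relative to Mann-Whitney the median split keeps (2/π)/(3/π) = 0.667. For a logistic-shaped outcome, the efficiency relative to Mann-Whitney is 3p(1−p).

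| Cut | Loss vs linear (normal) | Loss vs Mann-Whitney (normal) | Loss vs Mann-Whitney (logistic shape) |
|---|---|---|---|
| 50/50 | 36% | 33% | 25% |
| 40/60 | 38% | 35% | 28% |
| 30/70 | 42% | 40% | 37% |
| 20/80 | 51% | 49% | 52% |

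A 10/90 cut of a normal outcome loses 66% against a linear model. A pile-up at 100% was not examined. It is plausible, because {20c} fills blank later pages as 100%.

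**What that means for power, as an illustration.** At 184 per arm, a linear model has 80% power for a difference of 2.802 × √(2/184) = 0.292 SD. This effect is assumed, not taken from the article. For the same effect:

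- Mann-Whitney: effective n = 184 × 3/π = 175.7 per arm, power about 78%.
- Median split: effective n = 184 × 2/π = 117.1 per arm (368 × 0.637 = 234 in total), power about 61%.

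**A cut-off chosen from the data.** In 4,000 simulated trials with no effect and 184 per arm, a two-proportion z-test stood in for the arm term of the logistic model. A fixed median cut rejected in 4.9% of trials. Taking the best of five cuts (30th, 40th, 50th, 60th and 70th percentiles) rejected in 13.6%. Percentile cuts depend only on ranks, so this result does not rest on normality, provided ties are few.

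**The case against.** The strongest reply is that the logistic model need not touch TOTPAR. Patient-defined severe pain is a secondary outcome recorded as binary {18a}, neuropathic pain prevalence is another, and the trial is sized on a binary endpoint with an odds ratio. A reader might infer that no binary outcome exists, and that is wrong. But {20a} does not tie the model to severe pain, and if that is the intention, the primary outcome is left without adjustment.

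A reader might also infer that the primary comparison throws away a third of its information. It does not: Mann-Whitney uses the undichotomised scale. Only an adjusted analysis that dichotomises would lose information.

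Nor does the article plan a cut-off chosen after the data are in. That is a risk left open by the wording, and the full protocol or an analysis plan, not shown, may define the response in advance. The choice of a logistic model for a continuous score would still be a poor one.

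It is likewise an inference that the baseline comparison will pick the covariates. The two sentences stand next to each other, but the article does not link them. The number of baseline tests is not given either, so no error rate for them can be attached to this plan.

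Finally, {20a} and {20b} are in tension rather than plain contradiction. The logistic model is already declared in {20a}, and its wording can be read as a loose reference to prognostic factors.

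**Conclusion.** The point holds in a limited form. The article's only confounder-controlling model does not fit its continuous primary outcome, its response is undefined, and the stratification factors appear in no stated analysis. This is a mismatch in what is written, not only detail left to another document.

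The size is conditional. If TOTPAR is dichotomised, the adjusted analysis loses about a third of its information at a median split of a normal outcome, and about 25% to over 50% across the shapes and cut-offs examined. If the cut-off is picked from several, type I error could rise to about 14%. Both figures rest on assumptions, since the article gives neither a distribution nor a cut-off. The unadjusted Mann-Whitney result is not affected by either. This should be corrected, but it does not invalidate the main comparison.

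**What to change.** In {20a}, specify the adjusted analysis of the primary outcome as a linear or proportional-odds model of percent of maximum TOTPAR on arm, and choose between the two in advance. Proportional odds sits closest to the Mann-Whitney test and copes better with a ceiling at 100%. Fix the covariate list beforehand: surgery type and anaesthesia type as stratification factors, plus baseline variables such as PSQI, DN4, age and sex. Fit the model whatever the baseline table shows.

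Keep logistic regression for the binary severe-pain outcome. If a TOTPAR responder analysis is wanted as well, state its cut-off in advance and label it secondary.

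Present baseline data descriptively, and delete the statement that comparing them will identify bias.

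Say what is meant by response to the intervention. If effect modifiers are meant, specify arm-by-factor interactions, label them exploratory, and reconcile {20a} with {20b}. If prognostic factors are meant, reword the sentence.

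The cost is analysis wording. Surgery type, anaesthesia type, DN4, PSQI and demographics are already collected at inclusion {18a}, so no new data and no extra patients are needed.
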